### Statistical analyses

All statistical analyses will be performed using Statistical Analyses Software (SAS; version 9.4 for Windows, SAS Institute Inc., Cary NC, USA). Analyses on effectiveness of the intervention will be primarily done according to intention-to-treat methodology. Second, per-protocol analysis will be performed to analyze the efficacy of the intervention. All statistical tests will be two-sided and considered significant if *p* < 0.05.

Missing outcome data will be assumed to be ‘missing at random’ (MAR), conditional on key predictors of ‘missingness’ (in particular, baseline values of the outcome variables of interest, and study arm).

Patients’ sociodemographic and clinical variables will be compared at baseline between the three study arms using chi-square analyses for categorical variables and ANOVA for continuous variables and will be analysed as covariates.

Repeated measures analysis using generalised estimating equations, which account for the intra-patient dependency of the repeated measures, will be used to analyse the effect of the intervention on the outcome variables. We will investigate differences in effect of the two intervention arms and the arm receiving standard care at the different time points. Differential effects of the intervention arms by age, cancer subtype, and baseline levels of the outcomes of interest will be assessed for the outcome measures by adding terms for the interaction between age, cancer subtype, baseline levels, and care arm to the regression models.

Routinely collected data from the population-based NCR on patient and tumour characteristics will enable us to compare paper-and-pencil respondents with online respondents, as well as respondents with nonrespondents and patients with unverifiable addresses in order to determine the external validity of the results and answer our second study objective.

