**Methods/design:**

The LIVE randomised controlled trial consists of three arms: (1) standard care, (2) PRO feedback, and (3) PRO feedback and the *Living with lymphoma *intervention. Patients who have been diagnosed with Hodgkin lymphoma, non-Hodgkin lymphoma, including chronic lymphocytic leukaemia, as registered in the Netherlands Cancer Registry in various hospitals will be selected for participation. Patients are invited via their haemato-oncologist 6 to 15 months after diagnosis. The PRO feedback includes a graphical overview of patients’ own symptom and functioning scores and an option to compare their scores with those of other patients with lymphoma and a normative population of the same age and sex. The *Living with lymphoma *intervention is based on cognitive behavioural therapy components and includes information, assignments, assessments, and videos. Changes in outcomes from baseline to 16 weeks, 12, and 24 months post intervention will be measured. Primary outcomes are self-management skills, satisfaction with information, and psychological distress. Secondary outcomes are health-related quality of life, illness perceptions, fatigue, and health care use.

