### Randomisation

Patients who complete the baseline questionnaire online and consent to participate in the LIVE trial will be automatically randomised in an equal ratio (1:1:1) to one of the three study arms: (1) standard care, (2) standard care plus access to PRO feedback or (3) standard care plus access to PRO feedback and the *Living with lymphoma *intervention. This randomisation will be performed using block randomisation. The randomisation will be performed by a computer randomisation program which will ensure a balance in sample size across groups over time [29].

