### Sample size calculation

Sample size calculation was performed using G*Power version 3.1.9.2 for Windows. Based on the three primary outcomes of this trial, effect on patient level is defined as increased self-management skills or satisfaction with information (as measured by the heiQ^TM^ and the ISQ, respectively) or reduced psychological distress (as measured with the HADS). Therefore, effectiveness of LIVE is demonstrated when one of the three effects is statistically significant. Significance level of the sample size calculation was adjusted to *p* ≤ 0.167 to keep the overall chance for type-I errors at 5%.

Clinically important differences will be determined with Norman’s ‘rule of thumb’, whereby a difference of approximately 0.5 SD indicates a threshold of discriminant change in quality of life scores of a chronic illness [59]. To detect a clinically important difference with 90% power, a sample size of 222 patients with lymphoma (74 in each group) is needed. This sample size calculation is based on a medium effect size of 0.25 for repeated measures analysis of variance (ANOVA) with two measurements, since at least two measurements are necessary to compare preintervention and postintervention outcomes. We take into account a response rate of 70% as observed in earlier studies (of them 60% are expected to complete the questionnaires online) and a study dropout rate of 25%, based on a systematic review on adherence to Internet interventions for anxiety and depression [60]. This results in 663 patients with lymphoma who need to be invited for participation.

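### The any-one-of-three success rule promises 5% overall type I error, but the adjusted level is printed as 0.167, is tied only to the sample size, and the analysis tests everything at 0.05

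*Protocol article*

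**What the plan says.** The abstract of the protocol article names three primary outcomes: "Primary outcomes are self-management skills, satisfaction with information, and psychological distress".

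The Sample size calculation section sets the success rule: "effectiveness of LIVE is demonstrated when one of the three effects is statistically significant". It then deals with the multiplicity that this creates: "Significance level of the sample size calculation was adjusted to *p* ≤ 0.167", the stated aim being "to keep the overall chance for type-I errors at 5" per cent. The size follows from a "medium effect size of 0.25 for repeated measures analysis of variance (ANOVA) with two measurements", and the result is that "with 90% power, a sample size of 222 patients with lymphoma (74 in each group) is needed".

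The Statistical analyses section gives the rule for the tests themselves: "All statistical tests will be two-sided and considered significant if *p* < 0.05". It plans generalised estimating equations and looks at differences between the two intervention arms and standard care at the different time points. The article does not carry an adjusted level into this section or name another multiplicity procedure.

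**The concern.** A significance level used to compute a sample size does not control error. Only the level applied to the tests does. Two statements in the article therefore fail to support the promised 5%:

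- The level in the sample size section, as printed, is looser than 0.05 and cannot hold an overall 5% over three outcomes.
- The level in the analysis section is 0.05 for every test, under a rule that lets a single significant primary outcome carry the trial.

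An analyst who follows the analysis section could report LIVE as effective on one outcome with p = 0.03, while the article tells readers that the overall error is 5%. This touches the trial's main claim.

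**Working it through.** **Inputs from the article.** Three primary outcomes; success if any one is significant; overall error of 5% promised; printed adjusted level 0.167; analysis level 0.05 two-sided; effect size f = 0.25; two measurements; 90% power; 222 patients, 74 in each of three arms; clinically important difference about 0.5 SD.

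**Assumptions, not in the article.** The correlation between test statistics (0 to 0.9 tried) and the correlation between repeated measurements (mainly 0.5 and 0.7).

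**1. What the printed level delivers.** For three independent tests at level a, the overall error is 1 − (1 − a)³, with upper bound 3a.

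| Level per test | Independent | Upper bound |
|---|---|---|
| 0.167 (printed) | 1 − 0.833³ = 42.2% | 50.1% |
| 0.05 (analysis section) | 1 − 0.95³ = 14.3% | 15.0% |
| 0.05/3 = 0.0167 | 1 − 0.9833³ = 4.9% | 5.0% |

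Only the last row meets the stated aim.

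**2. Which level fits N = 222.** For the between-factors F-test in a repeated measures ANOVA with k = 3 groups, m = 2 measurements and correlation r, the noncentrality is f²·N·m / (1 + (m − 1)·r), with k − 1 and N − k degrees of freedom. N is raised in steps of 3 until power reaches 90%.

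| Level | N at r = 0.5 | N at r = 0.7 |
|---|---|---|
| 0.167 | 108 | 123 |
| 0.05 | 156 | 177 |
| 0.0167 | 198 | 222 |

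At 0.0167 and r = 0.7 the noncentrality with N = 222 is 0.0625 × 222 × 2 / 1.7 = 16.32. Power is 90.2%, and 219 patients fall just short at 89.7%, so 222 is reproduced exactly. At 0.167 no variant tried (between-factors, within-factors, interaction, one-way) needs more than 144. The printed level is therefore incompatible with the printed N in every model tried, while 0.0167 is compatible. The match is not unique: 0.0083 with r = 0.5 also gives 222.

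**3. Overall error under the analysis section, allowing for correlated outcomes.** Simulation of three equally correlated two-sided z-tests, 2 million draws, one test per outcome:

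| Correlation | Each at 0.05 | Each at 0.0167 |
|---|---|---|
| 0 | 14.3% | 4.9% |
| 0.3 | 13.6% | 4.8% |
| 0.5 | 12.5% | 4.4% |
| 0.7 | 10.9% | 3.9% |
| 0.9 | 8.4% | 3.0% |

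At 0.05 the error exceeds 5% throughout this range.

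**4. More than one test per outcome.** The heiQ is described as eight scales, there are two intervention arms, and there are three follow-up times. If only the two comparisons with standard care were tested for each outcome, six independent tests would give 1 − 0.95⁶ = 26.5% at 0.05 and 1 − 0.9833⁶ = 9.6% at 0.05/3. Dividing by three holds 5% only if each outcome contributes one test.

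**5. Power at 0.0167 with the planned numbers.**

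- Omnibus F-test as in step 2, N = 222: 93.9% at r = 0.5 and 90.2% at r = 0.7.
- Pairwise contrast of 0.5 SD, 74 per arm, normal approximation: power = Φ(0.5·√(74 / (2(1 − r²))) − 2.394), with r = 0 for no baseline adjustment. Unadjusted: Φ(3.041 − 2.394) = 74%. Baseline-adjusted at r = 0.5: Φ(3.512 − 2.394) = 87%. At r = 0.7: Φ(4.259 − 2.394) = 97%.
- For 90% power the same contrast needs about 108, 81 and 55 per arm respectively.

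**The case against.** The best defence is that the 0.05 sentence is a general default, that the sample size section shows the authors knew about multiplicity, and that a separate analysis plan may set the primary testing level. Some of this stands. The article does not show that the final analysis will use 0.05 for the primary outcomes, and it may well leave the choice of one scale, contrast and time point to a fuller document. That choice is not held against it here. But the sentence says that it covers all tests and makes no exception, so the conflict with the promised 5% is in the text and is not a gap.

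Three stronger readings are tempting and should not be taken.

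- A reader might infer that the sample size section uses a strict level which the analysis section then relaxes. As printed it does not: 0.167 is looser than 0.05 and lowers the required N. The strict level is an inference from the 5% aim and from the fit to 222, and that fit needs a correlation that the article does not state.
- A reader might infer that changing the analysis sentence alone, or naming Holm for three outcomes, secures 5%. It would leave 0.167 in print, and it does not hold 5% if an outcome contributes several tests.
- A reader might infer that the correction is free because 222 was already sized for it. That is supported for the omnibus F-test at the correlations shown, not for pairwise contrasts in general.

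**Conclusion.** The point holds. The article promises an overall type I error of 5% for an any-one-of-three claim, and neither level that it prints delivers this. At the 0.05 stated for the analysis, the error is 14.3% with three independent tests and 12.5% at an assumed correlation of 0.5, so roughly two and a half to three times the promise. These figures count one test per outcome, and further tests would add to them. The printed 0.167 would give 42.2% if used for independent tests. That it is a misprint of 0.0167 is probable but not proven. The inconsistency bears on the rule for the headline claim and should be settled before the final analysis.

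**What to change.** 1. In Sample size calculation, correct 0.167 to 0.0167 after checking it against the saved G*Power run, and state the test family and the correlation assumed. If the run used another level, restate N.
2. In Statistical analyses, replace the blanket sentence with wording such as: The three primary outcomes are tested at a family-wise two-sided level of 0.05 (0.05/3 each, or Holm's procedure), with one prespecified test per outcome that fixes the scale or score, the contrast or omnibus test, and the time point. All other tests use a two-sided 0.05 level without multiplicity control.

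Either 0.05/3 each or Holm meets the need. For the question whether at least one outcome succeeds they are equivalent, since Holm also compares the smallest p-value with 0.0167.

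**Cost.** A primary p-value between 0.0167 and 0.05 no longer suffices on its own. On the omnibus ANOVA basis, no patients are added at an assumed correlation of 0.5 to 0.7 (power 94% to 90%). If a pairwise 0.5 SD contrast is chosen, power with 74 per arm is about 74% unadjusted, and 87% or 97% with baseline adjustment at assumed correlations of 0.5 or 0.7. The article should state power for the test that it chooses.

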### Study design

The LIVE trial is designed as a nonblinded randomised controlled trial with three arms. For an overview of the design of the trial, see Fig. 1. Standard care plus the access to PRO feedback and the *Living with lymphoma *intervention (arm 3) will be compared to standard care plus access to PRO feedback (arm 2) and standard care (arm 1). Patients with lymphoma from various hospitals in the Netherlands will be included and asked to complete questionnaires at four points in time: baseline (T0; 6 to 15 months after diagnosis), after 16 weeks (T1; post intervention), after 12 months (T2), and after 24 months (T3).

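### Baseline significance tests between randomised arms are tied to an open covariate set, and the outcome's own baseline score is not placed in the main model

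*Protocol article*

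**What the plan says.** All the relevant text on the model is in the Statistical analyses section of the protocol article.

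- **Baseline comparison and covariates.** One sentence does both jobs: patients' "sociodemographic and clinical variables will be compared at baseline between the three study arms using chi-square analyses for categorical variables", with ANOVA for continuous ones, "and will be analysed as covariates". It contains no selection rule and no list. Study outcome measures names age, sex, date of diagnosis, histology, stage, treatment and comorbidity from the registry as examples of what is collected, and adds self-reported marital status, education and employment.
- **Main model.** "Repeated measures analysis using generalised estimating equations, which account for the intra-patient dependency of the repeated measures". The article does not say whether the baseline measurement is a response, a covariate or both.
- **Baseline score of the outcome.** It appears twice. Effect modification is to be assessed by "adding terms for the interaction between age, cancer subtype, baseline levels, and care arm to the regression models". Missing data are assumed missing at random given key predictors, "in particular, baseline values of the outcome variables of interest, and study arm".
- **Timing.** Under Study design, patients are "asked to complete questionnaires at four points in time: baseline (T0; 6 to 15 months after diagnosis"), then at 16 weeks (T1), 12 months (T2) and 24 months (T3). The abstract says: "Changes in outcomes from baseline to 16 weeks, 12, and 24 months post intervention will be measured".
- **Dropout.** The Sample size calculation section allows for 25%.

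**The concern.** There are two linked problems.

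First, the Randomisation section describes computer-generated block randomisation. Under it the null hypothesis of a chi-square or ANOVA test of baseline balance is true by design, so the result carries no information about whether to adjust. Because the sentence runs straight on to covariates, an analyst could take it as a rule to adjust for whatever turns out significant. The primary model would then be settled by the data, and a strongly prognostic variable that happened to be balanced would be left out.

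Second, the covariates are described only as sociodemographic and clinical. The baseline score of heiQ, HADS or ISQ is usually the strongest predictor of its own follow-up score, yet it is not placed in the main model. Two things are at stake: precision that the trial could have from data it already collects, and consistency with the plan's own missing-data assumption. An unweighted GEE is not valid under missing at random in general. It is valid when missingness depends only on covariates in the model. The plan names the baseline score as a driver of missingness but does not commit to having it there.

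**Working it through.** **Inputs.** From the article: three arms, 222 patients (74 per arm), effect size f = 0.25, two measurements, 90% power, measurements at T0 to T3. Not in the article: the correlation r between baseline and follow-up. It is assumed here to be 0.5 to 0.7.

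**Step 1: the plan's own figure.** For a repeated measures ANOVA, between-arm test, with m = 2 measurements:

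λ = f² × N × m / (1 + (m − 1) r), with df 2 and N − 3.

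The significance level is taken as 0.05/3 = 0.0167. This fits the stated purpose of a 5% overall error; the printed 0.167 does not (at r = 0.5 it would need only 108 patients).

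- r = 0.7, N = 222: λ = 0.0625 × 222 × 2 / 1.7 = 16.32, power 0.902. With 219 patients power is 0.897, so 222 is the smallest N with equal arms.
- r = 0.5: N = 198.

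So 222 is reproduced with r = 0.7. That value is inferred, not stated, but it suggests that the assumed range is not far from the planning.

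**Step 2: variance of the arm contrast at one follow-up time**, per patient, in units of σ²:

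- follow-up score only: 1
- change from baseline, or GEE with T0 as a response and free arm-by-time terms: 2(1 − r)
- baseline score as covariate, or T0 as a response with a common baseline mean: 1 − r²

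A generalised least squares calculation with four exchangeable time points gave the same values for the last two at T1.

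**Step 3: variance saved by adjusting for the baseline score.**

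Against change from baseline: 1 − (1 − r²)/(2(1 − r)) = (1 − r)/2. Against follow-up only: r².

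| r | against change: variance (standard error) | against follow-up only: variance (standard error) | against T0 as response, common baseline mean |
|---|---|---|---|
| 0.5 | 25% (13%) | 25% (13%) | 0% |
| 0.6 | 20% (11%) | 36% (20%) | 0% |
| 0.7 | 15% (8%) | 49% (29%) | 0% |

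The last column needs a working correlation that reflects the within-patient dependence. With working independence and a common baseline mean, the T1 contrast reduces to the difference in follow-up means (variance 1), and the follow-up-only column applies.

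**Step 4: how often the baseline tests mislead.** With 10 independent variables (an assumed number) tested at 0.05, the chance of at least one significant difference under sound randomisation is 1 − 0.95¹⁰ = 0.401, about 40%. This affects the primary model only if significant variables are the ones selected.

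**The case against.** The strongest case against the point has four parts.

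1. **Selection.** A reader might infer that covariates are chosen by the significance tests. The article does not say so. Grammatically the same variables are to be compared and to be used as covariates, with no threshold or condition, and the plain reading is that all of them are covariates. This stands. The criticism is that the sentence leaves both readings open and that under either one the list is not closed. Under the plain reading the 40% figure has no consequence for the model.
2. **Exclusion of the baseline score.** A reader might infer that it is left out of the main model. That reads silence as exclusion. T0 may enter the GEE as a repeated response, and the interaction models would normally carry a baseline main effect. This stands too, and a condensed article may leave such detail to the full protocol. But the article does specify covariates, by type, and names the baseline score only elsewhere, so the text as printed does not commit to using it.
3. **A fixed loss of 15-25% of precision.** A reader might take this as the cost of the plan. The documents do not support it. It is a variance figure, it needs an assumed r of 0.7 to 0.5, and it needs a change-score comparator. The abstract speaks of changes being measured, which describes the outcome and is no model; no change-score analysis is specified.
4. **Only a reporting matter.** Baseline tests create no bias by themselves. This is true of the tests alone. It does not answer the mismatch between the missing-data assumption and the model.

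**Conclusion.** The concern holds in a limited form. The article plans uninformative baseline tests, ties them to a covariate set that it does not close, and does not say that the outcome's baseline score is in the main GEE, even though its own missing-data assumption names that score. Depending on how T0 would otherwise enter, and for r of 0.5 to 0.7, the variance at stake runs from 0% to 49%. The width of that range is itself the reason to state the role of T0. These figures assume equal variances over time, complete data and a contrast at a single follow-up time. The missing-data argument assumes an unweighted GEE, since no weighting or imputation is mentioned. It is an improvement that should be made; nothing here shows that the planned analysis is invalid.

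**What to change.** 1. Replace the chi-square and ANOVA comparisons with a table describing baseline characteristics by arm, without p-values.
2. Give a closed list of covariates for each primary GEE, fixed before the comparative data are analysed and independent of observed balance. Include that outcome's baseline score, with T1, T2 and T3 as responses.
3. If T0 is preferred as a response, say so, constrain the baseline mean to be common across arms, and name a working correlation other than independence.
4. Keep the baseline-by-arm interaction in the separate effect-modifier model.
5. If a precision gain is quoted, give it as a range with the assumed correlation and comparator.

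The cost is wording only. The scores are collected at T0, the other variables come from the registry or the baseline questionnaire, and the article gives the trial status as recruiting.

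### The plan assumes data missing at random given baseline scores and arm, but does not say that the main GEE model conditions on the baseline score or uses weighting or imputation

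*Protocol article*

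**What the plan says.** All the relevant statements are in the protocol article.

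- **Assumption** (Statistical analyses): "Missing outcome data will be assumed to be ‘missing at random’ (MAR), conditional on key predictors of ‘missingness". The predictors are then named: "in particular, baseline values of the outcome variables of interest, and study arm".
- **Method** (Statistical analyses): "Repeated measures analysis using generalised estimating equations, which account for the intra-patient dependency of the repeated measures". The working correlation is not given, and neither weights nor imputation is mentioned.
- **Covariates** (Statistical analyses): the article lists sociodemographic and clinical variables here. Of these it says that they "will be compared at baseline between the three study arms using chi-square analyses for categorical variables and ANOVA for continuous variables"; they then serve as covariates. The Study outcome measures section describes clinical information as registry data (diagnosis, stage, treatment and so on), so this list does not read as including baseline questionnaire scores.
- **Baseline outcome levels** enter a model in one place only, the test of differential effects, by "adding terms for the interaction between age, cancer subtype, baseline levels, and care arm to the regression models".
- **Analysis set** (Statistical analyses): "Analyses on effectiveness of the intervention will be primarily done according to intention-to-treat methodology".
- **Expected loss** (Sample size calculation): "a study dropout rate of 25%, based on a systematic review on adherence to Internet interventions for anxiety and depression".

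The Study design section gives four measurement times: T0, 16 weeks (T1), 12 months (T2) and 24 months (T3). The article does not say whether T0 is one of the repeated outcomes or a covariate.

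**The concern.** The assumption and the estimator are both stated, but what would join them is not. The variable said to drive missingness, the baseline score, is not listed in the main arm-by-time model.

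Unlike a likelihood method, GEE on available data is not valid under missing at random in general. It is consistent in two standard cases: when data are missing completely at random, or when missingness depends only on covariates in a correctly specified mean model. Outside these, it relies on the working correlation being right.

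At stake is the comparison of arms at each time point, including 24 months. The trial is not blinded, and only arms 2 and 3 are shown their scores, so it is conceivable that high scorers leave one arm more readily than another. If they did, the patients remaining in that arm would score lower with no treatment effect. Analysing by intention to treat fixes who is counted in which arm; it does not repair missing follow-up.

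**Working it through.** **1. Where the plan's 25% enters.** The number to invite reproduces from 222 patients, 25% dropout, 60% online and 70% response:

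- 222 × 1.25 = 277.5, rounded up to 278
- 278 / 0.6 = 463.3, rounded up to 464
- 464 / 0.7 = 662.9, rounded up to 663, as stated

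So the 25% is used for numbers only. This does not settle the present point.

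**2. When GEE is consistent.** GEE solves Σ Dᵢ′ Vᵢ⁻¹ (Yᵢ − μᵢ) = 0 over observed visits. A sufficient condition is that E(Yᵢⱼ − μᵢⱼ) = 0 among those observed, given the covariates.

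- Baseline outcome and arm in the mean model, dropout depending on these alone: the condition holds for any working correlation.
- Baseline outcome not in the mean model: selection on baseline shifts the mean of those observed, and only V can correct it.
- Dropout also depending on T1 or T2 scores: a baseline covariate does not cover this, and V again matters.

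**3. Size, by large-sample simulation.**

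Inputs from the article: four visits, 25% lost (taken here as cumulative to T3), and the 0.5 SD threshold.

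Assumed inputs: no true effect; correlation 0.6 exchangeable or 0.75 first-order autoregressive (AR(1)); dropout logit slope 1 per SD in one arm against 0 or −0.5 in the other; dropout driven by arm with either the baseline score or the previous visit's score. There were 60,000 simulated subjects, an identity link, and simulation error of about 0.01 SD.

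Bias in the T3 arm difference, in SD (true value 0; ranges over the assumed slopes and true correlations):

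| GEE model | Dropout on baseline and arm | Dropout on previous score and arm |
|---|---|---|
| T0 as repeated outcome, independence | −0.208 to −0.094 | −0.236 to −0.130 |
| T0 as repeated outcome, exchangeable; truth exchangeable | +0.002 to +0.007 | −0.017 to −0.007 |
| T0 as repeated outcome, exchangeable; truth AR(1) | +0.054 to +0.062 | +0.023 to +0.026 |
| T0 as repeated outcome, unstructured | −0.025 to +0.001 | −0.019 to +0.007 |
| T0 as covariate, independence | −0.017 to +0.012 | −0.103 to −0.042 |
| T0 as covariate, exchangeable | −0.014 to +0.012 | −0.022 to 0.000 |
| T0 as covariate, unstructured | −0.015 to +0.012 | −0.011 to +0.008 |

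With slope 1 per SD in both arms, the T3 bias was within 0.014 SD of zero in every model. At T1, the first row's model gave −0.112 to −0.050 SD.

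**4. Scale.** The largest figure, 0.236 SD, is 0.236 / 0.5 = 47% of the plan's threshold. With 74 per arm, the standard error of an unadjusted difference is about √(2/74) = 0.164 SD, so it equals 0.236 / 0.164 = 1.4 standard errors. The negative sign follows from the assumed slopes and would reverse if they were exchanged between arms.

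**The case against.** The strongest reply is that this is a condensed article whose analysis plan is not shown. Working correlation, weights, imputation and the full covariate list commonly sit there. A reader might infer that the plan fixes an ordinary, unweighted GEE and therefore needs data missing completely at random. The text does not support that: it nowhere says unweighted, available-case or independence. Nor is missing completely at random required, because the missingness it names depends on baseline outcome and arm. With both in the mean model the bias is about 0 for every working correlation tried. The article also puts baseline levels into the interaction models, so it does not exclude them from modelling.

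The larger figures also need several conditions at once: dropout that depends on scores differently by arm, which no section documents; an independence working correlation, although the article stresses within-patient dependence; and no baseline covariate. The 25% comes from a two-measurement calculation, so spreading it to 24 months is itself an assumption. Preferring a mixed model over GEE is partly taste.

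All of this stands as a limit on how certain and how large the harm is. It does not join the two statements. The article gives an assumption, a method and a covariate list, and the baseline score is missing from that list. Its wording, "in particular, baseline values of the outcome variables of interest, and study arm", also leaves room for other predictors such as earlier follow-up scores, which a baseline covariate alone would not cover.

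**Conclusion.** The point holds in a limited form. As written, the main GEE analysis is not shown to be valid under the plan's own missing-data assumption. It is valid if baseline outcome and arm are in the mean model and dropout depends on nothing else. Otherwise the working correlation has to be right.

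Under the assumed arm-differential dropout, the T3 bias ranges from about 0 (unstructured correlation, or baseline-only dropout with baseline as a covariate) to about −0.24 SD (independence, no baseline covariate). If dropout depends on scores equally in all arms, it is about 0. These figures illustrate what is possible; they do not forecast this trial. They rest on assumed correlations, assumed dropout slopes and 25% loss accumulated by 24 months. It would be wrong to conclude that 25% dropout will bias the comparison: the article gives no evidence that dropout depends on scores differently by arm.

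**What to change.** State that the primary model for each outcome includes arm, visit, arm by visit and the baseline score of that outcome. Then choose one of two routes:

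- for continuous scores, a likelihood-based mixed model for repeated measures with unstructured covariance;
- if GEE is kept, inverse-probability-weighted GEE, or GEE after multiple imputation, with arm, baseline score and earlier follow-up scores in the dropout or imputation model.

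Conditioning on baseline alone would meet the assumption in its narrow form (baseline and arm only). Either route also covers dropout that depends on observed follow-up scores. Neither covers dropout that depends on scores never observed.

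The cost is a change of analysis text and program, a little more analysis work and a few more model parameters. The baseline score is already collected, both routes are available in SAS, which the plan already names, and no new data are needed.
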